#### The Action or Maintenance Stage

The chatbot will provide feedback and reinforcement based on participants’ PA level in the previous week. Positive reinforcement will be provided to participants who are on track to obtain or have already achieved the WHO-recommended MVPA level. This content aims to facilitate the maintenance of MVPA and to avoid relapse.

To prevent participants from watching the same video or reading the same information twice, slightly different videos/information corresponding to each SOC will be prepared. In each session, the chatbot will randomly select one for the participants. Participants in all stages can select one or more problems about PA from a list of common problems identified through a literature review and a focus group of older adults. Participants can also raise problems that are not on the list, verbally or in written form. The chatbot will retrieve relevant information from the knowledge graph and prepare a response.

### The Control Group

First, the chatbot will ask participants to fill out the Chinese version of the IPAQ-SF, automatically calculate their MVPA, and provide feedback based on the PA level. Second, the chatbot will automatically send a short web-based video covering general information of PA for older adults (eg, recommended MVPA level, suitable PA options) every week from week 1 to week 12. Finally, participants will select problems about PA from the same list in the intervention group. They will also have the option to verbally or in written form communicate any issues not included on the list. The chatbot will extract pertinent information from the same knowledge graph to craft a tailored response. Multimedia Appendix 4 shows the workflow of the control group.

If participants in the intervention or the control group provide no response to the intervention initiated by the chatbot within 24 hours, the chatbot will automatically send out 4 separate reminders. The project staff will proactively contact participants who provide no response to any reminders through WhatsApp or over the phone to identify reasons and solve problems.

### Measurements

#### Primary Outcome

Prevalence of meeting WHO-recommended levels of PA (at least 150 minutes of moderate-intensity aerobic PA, at least 75 minutes of vigorous-intensity aerobic PA, or an equivalent combination of MVPA every week) is the primary outcome. PA will be measured using the data provided by the participants in the Chinese version of the IPAQ-SF and from the accelerometers (ActiGraph) at T0, T1, and T2. After completion of the baseline telephone survey and before the randomization takes place, participants will be invited to visit our research office to collect the accelerometers. Onsite, participants will be instructed to wear the accelerometers on their waist (ie, above the right hipbone) with an elastic belt for 7 days, including 5 weekdays and 2 weekends, to collect objective data of PA levels. Participants will be asked to wear the accelerometers at all times except when they are showering or swimming. In addition, participants will be reminded to maintain their daily routine when they are wearing the accelerometers. Participants will visit our research office again 1 week afterward to return the accelerometers and recall their PA levels in the past week by completing the Chinese version of the IPAQ-SF. Similar procedures for collecting and returning accelerometers and completing the IPAQ-SF will be arranged after completion of the telephone survey at T1 and T2. The time on and time off related to accelerometer wearing each day will be recorded, and the data will be used to estimate the time spent in sedentary behavior, light PA, and MVPA. To ensure the accuracy of data that represent the habitual PA levels of participants, data from participants whose accelerometer-wearing time is less than 600 minutes per day will be considered invalid. We will calculate the sedentary time, light PA time, and MVPA time using triaxial cut points. The sedentary time, light PA time, and MVPA time have been defined as <200, <1951, and >1952 counts/minute, respectively, with the epoch length being 60 seconds [33]. The chatbot will automatically record the time spent by each participant with it.

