### Objectives

The proposed RCT will compare the efficacy of an SOC- versus a non-SOC-tailored intervention in increasing the prevalence of meeting WHO-recommended PA levels 6 months after completion of the intervention among inactive community-dwelling individuals aged ≥65 years. Given the strengths of chatbots in health promotion, both the SOC- and non-SOC-tailored interventions will be delivered by a chatbot with natural language processing (NLP) functions. The PA levels will be measured using the validated Chinese version of the International Physical Activity Questionnaire Short Form (IPAQ-SF) and accelerometers.

The secondary objectives of this RCT are to compare the following outcomes 6 months after completion of the intervention between the intervention and control groups: (1) minutes of MPVA, low-intensity PA, and sedentary time in the past week measured using both the IPAQ-SF and accelerometers; (2) step counts in the past week measured using accelerometers; (3) SOC levels, perceived pros, perceived cons, and perceived self-efficacy related to PA; (4) compliance to the web-based interventions; and (5) cognitive status.

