### Sample Size Planning

At T0, no participant will meet the WHO-recommended PA level according to the inclusion criteria. We assume that 10% of participants in the control group will meet the WHO-recommended PA level at T2 as there are minimum interventions. A target sample size of 97 per group (194 in total) would allow us to detect a between-group difference of 15% in the prevalence of meeting the WHO-recommended PA level at T2 (25% versus 10%; power=0.80, α=.05, PASS version 11.0 [NCSS Statistical Software]). We conservatively estimate the dropout rate to be 30% at T2. Thus, 139 eligible participants per group (278 in total) are required.

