### Statistical Analysis

Intention-to-treat analysis will be performed. The Markov chain Monte Carlo method will be used to impute missing primary and secondary outcomes. Variables to impute the missing values include participants’ background characteristics and baseline values of these outcomes. Chi-square and independent sample *t* tests will be performed to examine the between-group balance of potential confounders at baseline. We will compare between-group differences in primary and secondary outcomes at both T1 and T2. The relative risk, absolute risk reduction, and the number needed to be treated and their 95% CI values will be calculated using Microsoft Excel. Logistic regression for binary variables and linear regression models for continuous variables will be used to test between-group differences in primary and secondary outcomes after controlling for any baseline confounders, with *P*<.20 in between-group comparisons. IBM SPSS version 26.0 and R version 4.3.1 (R Foundation for Statistical Computing) will be used for data analysis, with 2-sided *P*<0.05 considered statistically significant.

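### The primary outcome is scored by two instruments with no rule on which one decides, so the 5% error rate and 80% power are tied to T2 but to no single test

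*Protocol article*

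**What the plan says.** The Objectives section sets one aim: "increasing the prevalence of meeting WHO-recommended PA levels 6 months after completion of the intervention among inactive community-dwelling individuals aged ≥65 years". It then adds: "The PA levels will be measured using the validated Chinese version of the International Physical Activity Questionnaire Short Form (IPAQ-SF) and accelerometers". The Abstract joins the two instruments in the same way.

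The Primary Outcome section defines a single prevalence and says "PA will be measured using the data provided by the participants in the Chinese version of the IPAQ-SF and from the accelerometers (ActiGraph"). It describes the wear period, a validity limit of 600 minutes of wear per day, and count cut points for sedentary time, light activity and MVPA. It gives no rule for turning two readings per participant into one yes/no result.

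Sample Size Planning powers one comparison at T2, 25% versus 10%. On the control rate it says: "We assume that 10% of participants in the control group will meet the WHO-recommended PA level at T2". No instrument is named there.

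Statistical Analysis says: "We will compare between-group differences in primary and secondary outcomes at both T1 and T2". It applies two-sided P<0.05 throughout, with no ordering of tests and no adjustment.

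**The concern.** A questionnaire and a device each classify every participant as meeting the level or not, and the two can differ. With no deciding rule, the T2 analysis yields two results with an equal claim to be the primary one. If only one is significant, the protocol cannot say whether the trial succeeded, and the choice could be made after the results are seen.

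The choice matters because the instruments differ in how open they are to bias. Under Baseline Survey and Randomization, participants are told their group; only assessors and analysts are blinded. Both arms complete the IPAQ-SF in the chatbot sessions and receive feedback on it. Reinforcement for reaching the target is described only for the intervention arm: "Positive reinforcement will be provided to participants who are on track to obtain or have already achieved the WHO-recommended MVPA level". A self-reported endpoint is therefore more exposed to differential reporting than a device that gives the wearer no feedback.

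**Working it through.** **Inputs.** From Sample Size Planning: 25% versus 10% at T2, power 0.80, α=.05, 97 evaluable per group, 30% dropout, 139 randomized per group. From Statistical Analysis: two-sided 0.05 for each test. The correlation between the two instruments' test statistics is not given; I assume 0 to 0.8.

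**1. The plan's own figure.** Normal approximation with unpooled variance:

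n = (1.960 + 0.842)² × (0.25×0.75 + 0.10×0.90) / 0.15² = 96.8, so 97 per group.

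Dropout: 97 / 0.70 = 138.6, so 139 per group. Both figures reproduce, for one two-sided test at T2.

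**2. Power of one test at 97 per group.** Using the pooled variance under the null, with mean proportion 0.175:

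power = Φ[(0.15 − 1.960 × √(2×0.175×0.825/97)) / √((0.1875 + 0.09)/97)] = Φ[(0.15 − 0.1069)/0.0535] = Φ(0.805) = 0.790.

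The exact binomial power of the same test is 0.802. The stated 80% is sound for a single test.

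**3. Either instrument at T2 may count, each at 0.05.** If independent, the chance of at least one false positive is 1 − 0.95² = 9.75%. For correlated tests I simulated pairs of standard normal statistics and counted how often either exceeded 1.96 in absolute value.

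**4. Both instruments must succeed at T2.** I assume the same 25% versus 10% on each, with power 0.790 per test. If independent, joint power is 0.7896² = 0.62. Otherwise it is the bivariate normal probability that both fall below Φ⁻¹(0.7896).

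| Assumed correlation | False positive, either counts | Power, both required |
|---|---|---|
| 0 | 9.75% | 0.62 |
| 0.3 | 9.5% | 0.65 |
| 0.5 | 9.0% | 0.67 |
| 0.8 | 7.8% | 0.72 |

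**5. What an explicit two-instrument rule would cost.** These sizes use the pooled formula, which gives 100 rather than 97 for the single test.
- Either may count, with α split to 0.025 each: 121 evaluable per group, and 121/0.70 gives 173 randomized per group (346 in total). Power per test at 97 falls to 0.70.
- Both required, 80% joint power: 131 to 116 evaluable per group for correlation 0 to 0.8, or 188 to 166 randomized per group.

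**6. Can the sample size section settle the instrument?** Only indirectly. Its premise that nobody meets the level at T0 rests on the inclusion criterion, which is screened with the IPAQ-SF (Participants and Recruitment). That points to the questionnaire, but the article never declares it the primary measure, and the Primary Outcome section presents the device as the source of objective data.

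**The case against.** The best defence is that the article states one primary outcome, not two, and one time for it. That stands for the time point. A reader might infer from the Statistical Analysis section that T1 and T2 results are both primary, making four tests and an error rate up to 1 − 0.95⁴ = 18.5%. The documents do not support this. The objective, the sample size and the expected result in the Discussion summary all name T2, so T1 reads as supportive. Nor does the article plainly announce two primary endpoints; the defect is a missing scoring rule, which leaves two candidate tests.

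A reader might also infer that questionnaire feedback is given to one arm only. It is not: The Control Group section describes the same in-chatbot IPAQ-SF with feedback. The outcome questionnaire is completed separately, at office visits, with blinded assessors. What remains is that participants know their group and that reinforcement for reaching the target is described only for the intervention arm. The documents give no basis for sizing any resulting bias.

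A further objection is that naming the accelerometer is not a mere relabelling. That stands. The 10% and 25% are not tied to the device, and the zero-at-T0 premise comes from the questionnaire screen. The cut points give one MVPA band and no vigorous threshold, so as described the device cannot score the vigorous or combined part of the WHO definition. The wear-time limit can also make data invalid beyond the 30% described as dropout.

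Finally, the questionnaire recalls the week in which the device is worn, so a high correlation is plausible and the lower end of the error range may apply. Even at 0.8 the rate is 7.8%, above 5%.

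**Conclusion.** The concern holds for the instrument and not for the time point. The sample size arithmetic is correct for one test at T2, but the plan does not say which test that is. If either instrument may count, the error rate is about 7.8% to 9.75%; if both must succeed, power at 97 per group is about 62% to 72%. These ranges rest on an assumed correlation of 0.8 to 0, and the power figures also on equal 25% versus 10% rates for both instruments. The measurement that defines the primary endpoint is what the sample size rests on, so it belongs in the protocol and should not be left to the analysis plan. It must be settled, because if the two instruments disagree at T2 the protocol cannot say whether the trial succeeded.

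**What to change.** Before unblinding, amend the protocol, any analysis plan and the registry entry as follows.

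- Name one instrument at T2 as the single primary test, at two-sided 0.05.
- Make the other instrument at T2 the first secondary endpoint, tested only if the primary is significant.
- State that all T1 comparisons are supportive.
- State the assumed control and intervention rates for the chosen instrument.

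The accelerometer is the preferable choice, because participants know their group and self-report is more open to differential reporting. If it is chosen, Sample Size Planning must re-justify the 10% and 25% rates and the premise of zero at T0 for the device. The WHO level must be expressed in what the cut points can score, and the loss allowance must cover recordings that fail the wear-time limit. If the IPAQ-SF is kept as primary, report the accelerometer result alongside it as the key check on reporting bias.

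Naming one instrument does not in itself change the 139 per group, provided the rates and loss allowance hold for it. The cost is the amendment, the re-justification if the device is chosen, and that only one instrument carries the confirmatory claim. If the sponsor prefers an either or both rule, it must be written down with the matching α split or the larger sample shown in the working.

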#### Secondary Outcomes

The following secondary outcomes will be measured at T0, T1, and T2:

Step counts and minutes of MVPA, light PA, and sedentary time in the past week measured using accelerometers.Compliance with the web-based interventions, including the number of intervention sessions started and completed, as documented by the chatbot.The SOC related to the PA measured using a validated multiple-choice question [34]. The measurement and definition of the SOC will be the same as those used by the chatbot. In addition, we will extract the SOC measured by the chatbot at the beginning of each intervention session in the intervention group from the chat history.Perceived pros and cons related to PA will be measured using the validated questionnaire on decisional balance developed by Nigg et al [35], which consists of 10 questions with 2 scales (pros and cons).Perceived self-efficacy of PA will be measured using a validated 6-item scale developed by Marcus et al [34].Cognitive status will be measured using cognitive tasks, including the sustained attention test [36], working memory [37], inhibitory control [38], and cognitive flexibility [39].

The outcome assessors and data analysts will be blinded to the treatment allocation. Participants will be reminded not to disclose the intervention they receive to assessors.

### Safety Issues and Adverse Events

Participants can report adverse events related to PA through WhatsApp or a hotline during the study period. If sustained serious adverse events are found, advice will be sought from a sport science expert.

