## Methods

### Study Design

This is a partially blinded (outcome assessors and data analysts) and parallel-group RCT to be conducted in Hong Kong, China. Inactive community-dwelling people aged 65 years or more will be randomized evenly (1:1) into either an intervention group or a control group. In the intervention group, the chatbot will measure participants’ SOC related to PA and deliver web-based interventions tailored to their current SOC every week for 12 weeks. In the control group, the chatbot will not measure participants’ SOC but will deliver a standard and non-SOC-tailored web-based intervention every week for 12 weeks. Participants will be interviewed at baseline (T0), after completion of the intervention (T1), and 6 months after T1 (T2). The study was registered at ClinicalTrials (NCT06641492). The study flowchart diagram is shown in Figure 1. We will report this trial in accordance with the CONSORT-EHEALTH (Consolidated Standards of Reporting Trials of Electronic and Mobile Health Applications and Online Telehealth) checklist (Multimedia Appendix 1) [31] and the SPIRIT (Standard Protocol Items: Recommendations for Interventional Trials) checklist (Multimedia Appendix 2).

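### The only adverse event route the article describes is participant-initiated and limited to activity-related events, so harms are likely to be under-counted and a low count could not be read as evidence of safety

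*Protocol article*

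**What the plan says.** The section Safety Issues and Adverse Events in the protocol article consists of two sentences. The first gives the route: "Participants can report adverse events related to PA through WhatsApp or a hotline during the study period". The second gives the action: "If sustained serious adverse events are found, advice will be sought from a sport science expert". No step for finding such events is described.

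The population is set out under Study Design: "Inactive community-dwelling people aged 65 years or more will be randomized evenly (1:1) into either an intervention group or a control group".

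The same section schedules interviews of all participants at T0, T1 and T2. Under Primary Outcome, each assessment also includes a telephone survey and office visits to collect and return the accelerometer. Secondary Outcomes opens its list with "The following secondary outcomes will be measured at T0, T1, and T2". The list covers accelerometer measures, compliance, stage of change, pros and cons, self-efficacy and cognition. Adverse events are not on it, and Statistical Analysis does not mention them. The same section says that outcome assessors are blinded.

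Two other contacts matter here. In each weekly session, participants in both arms can pick problems about physical activity from a list or raise their own. For those who do not answer the chatbot, the section The Control Group (in a paragraph covering both arms) says: "The project staff will proactively contact participants who provide no response to any reminders through WhatsApp or over the phone to identify reasons and solve" any difficulties.

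**The concern.** The article states a method here, and the method has two filters. The participant must start the report, and must first judge that the event was related to physical activity. A fall at home or a hospital admission that the participant does not connect with exercise falls outside the stated rule, even if a blinded reader of both arms' data would want it counted.

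The timing adds to this. The 12 weekly chatbot sessions fall within about 3 months, and T2 comes 6 months after T1. For most of follow-up there is no weekly session that might prompt a report.

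What is at stake is the meaning of a low count. The trial encourages inactive older people to do moderate-to-vigorous activity, and the Conclusion foresees use in existing community WhatsApp groups. A report of few or no adverse events could be taken as reassurance when it may partly reflect how events were collected. The primary efficacy result is not affected.

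**Working it through.** **Routes set side by side**

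| Contact described | Who starts it | Stated purpose | Harms asked about? |
|---|---|---|---|
| WhatsApp or hotline report | Participant | Activity-related adverse events | Only what is volunteered |
| Weekly chatbot session, both arms | Chatbot | Intervention, problems about activity | Not stated |
| Staff call to non-responders, both arms | Staff | Reasons for non-response | Not stated |
| T1 and T2 telephone survey and office visits | Staff | Primary and secondary outcomes | Not listed |

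Only the first row is described as a way of capturing adverse events. The second and third could bring an injury to light by chance. The fourth is systematic, reaches both arms on the same schedule and is not described as used for harms.

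**The plan's own figure**

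The article gives no adverse event figure. The arm size used below is the planned 139 from Sample Size Planning, which reproduces:

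- (1.96 + 0.8416)² × (0.25 × 0.75 + 0.10 × 0.90) / 0.15² = 96.8, rounded up to 97
- 97 / (1 − 0.30) = 138.6, rounded up to 139

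**Illustration of the under-count**

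The true risk p per participant and the capture probability c are assumptions; neither is in the document. Expected recorded events in an arm are 139 × p × c. The chance of recording none is (1 − p × c)^139.

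| Assumed p | c = 1.0 | c = 0.7 | c = 0.6 | c = 0.3 |
|---|---|---|---|---|
| 1% | 1.4 expected, P(none) 25% | 1.0, 38% | 0.8, 43% | 0.4, 66% |
| 2% | 2.8, 6% | 1.9, 14% | 1.7, 19% | 0.8, 43% |
| 5% | 7.0, 0.1% | 4.9, 0.7% | 4.2, 1.4% | 2.1, 12% |

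For p = 2%: 0.98^139 = 0.060, 0.986^139 = 0.141, 0.988^139 = 0.187 and 0.994^139 = 0.433.

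The c = 0.7 column is a rough benchmark for the proposed question, because the article assumes 30% dropout at T2 and those participants would not answer it. The realistic comparison at p = 2% is therefore 14% against 19% to 43%. Measured against 6%, the gain would be overstated.

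**Illustration of unequal reporting between arms**

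Assume a true 10% in both arms, which is 13.9 events per arm. If 60% are reported in one arm and 40% in the other, the counts are 13.9 × 0.6 = 8.3 and 13.9 × 0.4 = 5.6, an apparent ratio of 1.5 with no true difference. Conversely, a true 15% against 10%, reported at 40% and 60%, gives 139 × 0.15 × 0.4 = 8.3 and 139 × 0.10 × 0.6 = 8.3, and the excess disappears. This shows what unequal reporting would do. It is not evidence that reporting will be unequal.

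**The case against.** The strongest reply is that this is a condensed article. It says that participants can report, not that this is the sole route. Its measurement sections list efficacy outcomes and do not reproduce the interview form. The checklists and workflows are in appendices that are not shown, and a fuller protocol could contain a falls or injury item. A reader might infer that nobody will ask about harms, and the article does not support that. Weekly sessions in both arms invite problems about activity, and staff contact those who go silent, who may include someone who has been injured. What survives is narrower: the article does state a method, and that method is volunteered and filtered by attribution.

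A reader might also infer that the counts will depend on how engaged each arm is, because WhatsApp both delivers the intervention and carries reports. The documents do not support that as a fact. Both arms have the same platform, weekly sessions, problem list, reminders and staff follow-up, and the hotline needs no chatbot use. Engagement is an outcome still to be measured: "Compliance with the web-based interventions, including the number of intervention sessions started and completed, as documented by the chatbot". The article plans no between-arm comparison of harms. Differential reporting is a possibility only.

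Two further points are fair. Anyone scoring 1 or more on the PAR-Q is excluded, which lowers expected harms without changing how they are captured. Harms are not a stated objective, and no figure in the plan is wrong on this account.

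**Conclusion.** The point holds in a limited form. The only adverse event route described is spontaneous reporting of events the participant links to physical activity, and the listed T1 and T2 measurements include no harms item. Followed as written, this is likely to under-count falls, injuries and admissions, and few recorded events could not be read as evidence of safety.

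The size cannot be computed from the document. Every rate in the illustrations is assumed, and the result is sensitive to both the true risk and the capture probability.

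The conclusion assumes that no solicited harms question exists in material not shown; if one does, the point falls away once the article says so. Primary outcome, sample size and efficacy analysis are untouched. It is worth acting on because the remedy is cheap, not because a result is invalid.

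**What to change.** At the existing T1 and T2 interviews, ask both arms the same short closed question: any fall, injury or hospital admission since the last contact, whether or not the participant thinks it was related to activity. Have the blinded assessors ask it in fixed wording. Tabulate the answers by arm, and show volunteered WhatsApp and hotline reports separately as a second source. If the full protocol already contains such a question, state it in the safety section.

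The costs are about a minute of interview time and more events to log. No visit is added and the sample size does not change. Three limits remain:

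- Recall runs over up to 6 months at T2.
- Dropouts, assumed at 30% by T2, give no answer.
- Follow-up at T1 began in March 2025, with 185 participants already randomized by the end of February. If the question is added after that, some T1 interviews will lack it. The date of introduction and the number of participants asked in each arm must then be reported, and T1 counts read with that in mind.
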